### Provisions for post-trial care 

Due the nature of the intervention and the general health status of the participants, no special post-trial care will be required. In the unlikely event of persistent study-related complications, any damages will be covered by the study insurance.

### Outcome assessment 

The follow-up examinations will be conducted by an independent examiner blinded to the tenodesis technique received by the study patient (observer-blinded).

#### Primary outcome measure

The *primary endpoint* will be the biceps-specific LHB score as assessed at 12 months after surgery. The score will also be recorded at baseline and at the 6-week, 6-month, and 24-month follow-ups. This highly disease-specific assessment of LHB-associated outcome after surgery includes patient-reported symptoms (pain, cramps, or tenderness), the cosmetic result (Popeye deformity), and an objectively measurable functional parameter (flexion strength), each compared to the healthy contralateral tendon [25], with patient-reported outcome weighted more heavily in the overall score than functional outcome [25, 26]. The LHB score has been shown in previous studies to be a valuable tool for evaluating outcome after LHB tenotomy and tenodesis procedures [17, 25–30].

#### Secondary outcome measures

*Assessment of safety:* Another part of the hypothesis of the trial is that implant-free loop tenodesis is associated with fewer implant-related complications. A core set of adverse events of special interest has been set up for this study (see Table 2).

While intraoperative complications will be assessed during the performance of the randomized procedure, postoperative adverse events of special interest will be specifically queried at each follow-up visit. Such events will be graded according to the modified Clavien-Dindo classification for orthopedic surgery [31], depending on the need for outpatient or surgical/inpatient treatment. Since the overall complication rate is expected to be low, as seen in previous trials [9, 12], differences in the complication rates were not considered a primary endpoint and were thus not included in the sample size calculation.

For the selection of *secondary outcome parameters*, we followed the suggestions for comprehensive patient assessment in clinical trials on shoulder surgery by Wright and Baumgarten [32] for the American Academy of Orthopedic Surgeons to combine general health outcome measures with general shoulder function measures and disease-specific shoulder measures. Since the disease-specific LHB Score was chosen as the primary outcome parameter, we added the following general health and general shoulder function measures as secondary outcome parameters:The Constant(-Murley) score and the ASES score (American Shoulder & Elbow Surgeons Society standardized Shoulder Assessment) were chosen for the assessment of global shoulder function because they are the first and second most frequently used shoulder function scores in the world [33]. Both scores will be part of each study visit.The disability of arm, shoulder, and hand (DASH) score serves as an evaluation tool of global function of the arm at each study visit. The score is recommended when more than one joint of the arm is affected, as is the case with pathologies of the biceps brachii.For the assessment of general health-related quality of life at each study visit, we chose the SF-36 questionnaire as another standard score in the related literature.Strength measurements: Elbow flexion strength is measured using an isometric dynamometer (IsoForce-Control®, Herkules Kunststoff AG, Oberburg, Switzerland) with the patient seated in a chair, 90 degrees of elbow flexion, and a supinated forearm. The patient is then instructed to pull on the loop attached to the isometric dynamometer. Moreover, forearm supination strength is examined using the Baseline hydraulic wrist dynamometer (Fabrication Enterprises Inc., White Plains, NY, USA) with the elbow immobilized in 90-degree flexion by a motion control splint. The patient is instructed to supinate the forearm with maximum force against a T-handle from a neutral position. All measurements are repeated three times, and a mean value is calculated. Both flexion and supination strength are assessed and compared to the unaffected contralateral arm as a secondary parameter. Strength assessment will start from the 6-month postoperative follow-up visit.B-mode ultrasound examination of the LHB tendon in the bicipital groove will be part of each follow-up visit to assess the structural integrity of the tenodesis construct at any time after surgery. It is performed in the transverse and longitudinal planes, and ultrasonographic images are locally stored for later comparison and measurement. To objectify this investigator-dependent diagnostic tool for later evaluation, the answering of several standardized binary questions (yes/no) will be mandatory.MRI examination is required to evaluate tendon ingrowth into the surrounding connective tissue at the attachment site at the final follow-up visit after 2 years, since MRI is considered the unbiased gold standard in tendon diagnostics.

### Participant timeline

The following baseline data will be collected for each study patient after written informed consent has been obtained: age, sex, height, weight, arm dominance, American Society of Anesthesiologists (ASA) grade, concomitant diagnoses and medications, previous arm surgery, and tobacco and alcohol use. All functional outcome scores will be assessed at enrollment prior to surgery to obtain preoperative scores.

After the allocated study intervention has been conducted, patients will be seen for follow-up examinations at four postoperative visits (after 6 weeks, 6 months, 12 months, and 24 months) to evaluate the study outcome parameters (see Table 1).

### Sample size calculation 

The primary objective of this study is to show the non-inferiority of loop tenodesis in comparison with arthroscopic anchor tenodesis with respect to the primary clinical outcome LHB score (scale range 0–100). The clinical non-inferiority margin was set at 5 points on the LHB score, which was based on statistical considerations and clinical judgment. Moreover, an expert panel of German-speaking shoulder surgeons was consulted on the study design and the choice of non-inferiority margin. The panel defined a non-inferiority margin of 5 points, taking into account the differences in LHB scores between the established procedures and the minimal clinically important differences in other related scores. For loop tenodesis to be considered standard of care and to show non-inferiority to implant-based tenodesis techniques, it has to outperform the technically easier procedure of biceps tenotomy. According to Kerschbaum et al. [26, 34], the mean LHB score of patients treated with biceps tenotomy is at least 5 points lower than that of patients treated with arthroscopic epiosseous suprapectoral anchor tenodesis. Setting the non-inferiority margin at 5 points can also be considered a benchmark for outperforming biceps tenotomy as a historical control, as suggested by studies by Kerschbaum et al. [26, 34]. Moreover, according to the literature [17, 25–28], we expect a mean LHB score of 85 with a standard deviation of 10 for both treatment groups at 12 months. The non-inferiority margin of 5 points is half of the expected standard deviation, which is widely accepted as the minimal clinically relevant difference of PROs [35]. To show non-inferiority with a non-inferiority margin of 5 points and a standard deviation of 10 points with a power of 90% at a one-sided 2.5% level of significance, a total of *n* = 172 patients are required for statistical analyses. Assuming an early drop-out rate of 10% (change of indication during arthroscopy and thus no need for surgery or no information on the clinical outcome (drop-out before week 6)), a total of *n* = 192 patients (96 per group) need to be randomized. Sample size was calculated by using SAS 9.4 and the procedure proc power.

### Recruitment 

Different measures were taken to minimize recruitment challenges and to improve adherence to interventions:The selected inclusion and exclusion criteria are not overly restrictive and therefore allow the recruitment of the majority of patients with the tendon pathologies of interest at the enrolling centers.There are no competing trials at the enrolling centers, so that all eligible patients can be enrolled in this trail without confounding factors. Since there is no seasonal fluctuation of the incidence of LHB pathologies, constant recruitment throughout the entire recruitment period is possible.To reduce the complexity of the protocol, we chose a simple two-arm, parallel group design, omitting a third control group treated with simple tenotomy. Within the control group, a single tenodesis technique was clearly defined as the appropriate comparator.

### Assignment of interventions: allocation 

Allocation to one of the two treatment arms in a 1:1 ratio will be randomized using block-wise randomization with different block sizes stratified by center. The randomization list and the block size will be concealed for all participants until the final endpoint has been analyzed. Randomization will be carried out using the clinical database management system (CDMS) managed by the Center for Clinical Studies at the University Hospital Regensburg. After a patient has been enrolled by signing the informed consent and on the day of surgery, the responsible personnel (investigator and/or study nurse) must use the individual login for the CDMS to randomize the patient. All randomizations will be logged and documented within the system, and predefined users such as the study monitor will be automatically informed about the randomization.

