## Interventions

### Intervention description 

Both surgical and perioperative treatment will be conducted by the enrolling center. The patient is placed in a standard position for arthroscopic surgery of the shoulder. After preparation of the surgical field using standard procedures in accordance with current recommendations [19], the required standard arthroscopic portals are created. Since both the experimental intervention and the control intervention can be performed using the same skin incisions, blinding of the patients to the treatment received is possible. The surgical procedure starts with diagnostic arthroscopy to confirm structural lesions of the LHB complex and concomitant pathologies. After diagnostic arthroscopy is finished, the randomized trial intervention of implant-free loop tenodesis (experimental intervention) or implant-based epiosseous anchor tenodesis (control intervention) is performed, regardless of the concomitant pathologies.

The study groups differ in the details on how the LHB tendon is reattached to a less stress-exposed area at the humeral head after the tendon is cut at its origin. While the control treatment uses an implant for secure fixation, the trial intervention does not require an implant:

*Experimental Intervention Group: Loop tenodesis technique*
First, the intended position for tendon fixation at the entrance to the bicipital groove is debrided to create a slightly bleeding surface for improved tendon ingrowth. The LHB tendon is then securely grasped with a surgical clamp and cut close to its base. Afterwards, the tendon stump is pulled extracorporeally. About 5–15 mm of the injured proximal tenotomized tendon is then resected. The tendon “loop” is created extracorporeally by folding and doubling the proximal 1.5 cm of the LHB tendon stump in order to increase the proximal diameter of the tendon. The loop is fixed with a suture. After completion of the loop, the tendon is released and pushed intraarticularly. The tendon loop then locks into place at the previously debrided entrance to the bicipital groove, where it should gradually grow in.
*Standard of Care Intervention Group: Arthroscopic epiosseous anchor tenodesis technique*

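### Allocation appears to precede the arthroscopy that confirms the indication and is not withheld from the surgeon, so change-of-indication losses fall after randomisation, and the protocol is inconsistent on whether these patients are analysed

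*Protocol article*

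**What the plan says.** Protocol article, Assignment of interventions: allocation. The timing is given as "After a patient has been enrolled by signing the informed consent and on the day of surgery, the responsible personnel" use a personal database login to randomise. Those personnel are an investigator and/or a study nurse. Study setting says that all investigators are shoulder surgeons.

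Intervention description. "The surgical procedure starts with diagnostic arthroscopy to confirm structural lesions of the LHB complex and concomitant pathologies"; the randomised technique follows once that step is finished. Both techniques use the same skin incisions, and Explanation for the choice of comparators adds that they use the same portals.

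Sample size calculation. "172 patients are required for statistical analyses", and 192 are to be randomised. The 20-patient gap is explained by a 10% early drop-out, one cause of which is "change of indication during arthroscopy and thus no need for surgery". The other cause is loss of outcome information before week 6. No split between the two is given.

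Who will be blinded. Two levels are named, patients and outcome assessors.

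Statistical methods. The primary estimand covers all randomised patients with an LHB score at any time. Missing month-12 scores are multiply imputed under MCAR or MAR. Participant timeline and Table 1 place the first LHB score at enrolment, before surgery.

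**The concern.** The check that can remove a patient's need for tenodesis takes place after the patient has been allocated. It is made by a surgeon who is not blinded and who may have done the randomisation. A judgement made at that point can differ between arms even when nobody intends it. The loop is formed by folding the patient's own tendon stump, whereas the control uses a suture-armed tendon and an anchor, so the state of the tendon might weigh differently on a surgeon who knows the arm. That mechanism is an inference; the protocol does not describe it.

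What is at stake is the primary comparison. If the affected patients leave the analysis, exclusion rests on a post-randomisation decision open to influence. If they stay, they contribute outcomes without a tenodesis or imputed values, which tends to make the arms look alike in a non-inferiority trial. The protocol does not settle which of the two happens.

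**Working it through.** **1. The plan's own figures.** The inputs, all from Sample size calculation, are: margin 5, SD 10, mean 85 in both arms (true difference 0), one-sided 2.5%, power 90%. The exact two-sample t-test has power 0.8999 at 85 per arm and 0.9032 at 86 per arm, so 86 per arm = 172 are needed. Then 172/0.90 = 191.1, which gives 192 (96 per arm). Both stated figures reproduce, so the sample size arithmetic is not at fault.

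**2. Order of events.** The allocation section says only that randomisation is on the day of surgery. The sample size section lists change of indication at arthroscopy as a loss between 192 randomised and 172 analysed. A randomised patient can be lost for that reason only if randomisation came first. The order is therefore inferred, but no other order fits the calculation.

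**3. Who is analysed.** Set side by side:
- Sample size calculation: change-of-indication patients belong to the 20 not available for analysis.
- Statistical methods with Participant timeline: any randomised patient with one LHB score is in the population, and the baseline score exists before surgery. Read literally, these patients are in.

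The two statements need reconciling.

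**4. If they are dropped (illustration).** Assumptions, none from the protocol: a fraction f of an arm is removed outright, removed patients would have differed from their arm mean by 10 points, about 86 per arm are analysed, and the true difference lies exactly at the margin.

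Shift in the remaining mean = 10f/(1 − f). SE = 10 × √(2/86) = 1.525. One-sided error = Φ(−1.96 + b/1.525), where b is the net shift in favour of loop.

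| Removed, loop v anchor | Removed patients would score | b | Error at margin |
|---|---|---|---|
| equal | lower or higher | 0 | 2.5% |
| 6% v 4% | lower | 0.64 − 0.42 = 0.22 | about 3.5% |
| 7.5% v 2.5% | lower | 0.81 − 0.26 = 0.55 | about 5.5% |
| 15% v 5% | lower | 1.76 − 0.53 = 1.24 (before rounding of the terms) | about 12.6% |
| 15% v 5% | higher | −1.24 | about 0.3% |

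The 15% v 5% row is an upper scenario: it assigns the whole 10% allowance to change of indication, with a threefold imbalance. The 7.5% v 2.5% row assigns half of it.

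**5. If they are kept.** Suppose 5% to 10% of each arm have no tenodesis and the same mean outcome in both arms (assumed). A true deficit of 5 points then appears as 5 × 0.95 = 4.75 to 5 × 0.90 = 4.5 points. This direction always favours non-inferiority.

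**6. Sample size after later randomisation.** With a remaining early drop-out d, the requirement is 86/(1 − d) per arm, rounded up: 192 in total at 10%, 186 at 7.5%, 182 at 5%, 172 at 0%. Without the split of the 10%, no point in this range can be chosen.

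**The case against.** The strongest reply is that the protocol shows an opportunity and nothing more. The lesion is already confirmed on MRI before enrolment. Both techniques are routine at every centre, and both cut and reattach the same tendon, so nothing suggests that the need for tenodesis depends on the arm. The surgeon must document the tendon pathology seen at operation, the DSMB verifies randomisation and blinding, and eligibility and randomisation receive full source data verification. No section says when the surgeon learns the arm, and the article condenses a longer protocol.

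Much of this stands. The safeguards make selective exclusion easier to detect, but they do not prevent it. That the surgeon knows the arm during arthroscopy is not stated; it is only not ruled out.

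Three stronger readings are tempting and are not supported:
- That every route favours non-inferiority. Dilution does. Selective removal has no fixed direction, because nothing says that patients without an indication would score lower.
- That 12.6% is the error rate of the planned analysis. It assumes outright deletion, one sign and a threefold imbalance, whereas the stated population literally keeps patients with a baseline score and imputes month 12. Imputation does not guarantee freedom from bias, but it is a different analysis.
- That later randomisation would raise power to 93%. That figure needs all 96 per arm to be analysable. Losses before week 6 would remain, and if the 10% inflation is kept for them, 172 analysed and 90% power are what result.

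**Conclusion.** The point holds as a design weakness with an inconsistency attached. On the protocol's own account, change-of-indication losses arise after randomisation, at a step where the surgeon may know the arm, and two sections disagree on whether those patients are analysed. The documents do not show that selective exclusion will occur.

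The size is uncertain and depends on assumptions about imbalance and prognosis that the protocol cannot supply. Under those assumptions and outright removal, the one-sided error ranges from about 0.3% to about 12.6%, and is 3.5% to 5.5% for the two smaller imbalances when removed patients would score lower. The sample size is correct as computed, and no power gain can be claimed. The change is worth making because it is cheap and closes the route altogether.

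**What to change.** Release the allocation in the database only after diagnostic arthroscopy has confirmed the biceps tendon indication, and before any arm-specific step. In the loop arm the groove is debrided before the tendon is cut, so release should precede both. Record patients without an indication as screening failures. State separately how much of the 10% allowance is for loss before week 6.

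If allocation must stay earlier, reconcile Sample size calculation with Statistical methods by stating that all randomised patients are followed and analysed, and report change of indication by arm.

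Cost: a protocol amendment and a small change in theatre workflow, with staff opening the allocation during the operation and the anchor at hand for every case. The shared portals, the common diagnostic step and the existing same-day database randomisation make this feasible.

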## Assignment of interventions: blinding

### Who will be blinded 

The trial includes two levels of blinding:Trial participants will be blinded to their treatment allocation. This blinding is intended to reduce the risk of treatment-related behavior and patient awareness of treatment-related side effects. As the surgical treatment in both study groups can be performed using the same skin incisions and the implants in the control group are not visible in plain radiographs, patients will not be able to identify the treatment they have received (*patient-blinded*).To avoid detection bias during the study visits, collection of the postoperative outcome parameters will be conducted by outcome assessors who are not aware of the treatment allocation and have not been included in the surgical procedures (*outcome assessor-blinded*).

### Procedure for unblinding if needed 

Unblinding is not necessary in any circumstances during study participation, since even in case of adverse events or need for revision surgery, continued blinding of both patients and outcome-assessors is feasible. Of course, unblinding of participants and study personnel is permissible, if patients withdraw consent to participate in the study.

## Data collection and management

### Data management strategy 

To facilitate the collection of study data, a web-based electronic case report form (eCRF) will be established within a clinical database management system (CDMS). This system will provide a comprehensive, auditable, and integrated environment that meets the regulatory requirements of ICH E6 (R2) and GDPR. Each investigator is responsible for reviewing and ensuring the accuracy, completeness, and timeliness of the pseudonymized patient data entered into the eCRF and will provide his/her signature and date of signature on the eCRF pages. During the study, monitors will review the eCRF entries by remote, and if necessary, by onsite source data verification in order to ensure accuracy, completeness, and plausibility of the data entered. Data entered into the study database will be systematically and periodically checked by senior data management staff for completeness, omissions, and values requiring further clarification, using computerized and manual procedures. In addition, a central statistical monitoring approach will be applied to improve data quality and site performance. Any errors or omissions are recorded on data query forms, which are forwarded to the study site for resolution. Quality control audits of all key safety and efficacy data in the database are made prior to locking the database. After study completion, all electronic study data will be converted into an auditable and system-independent accessible standard data format (CDISC) and stored for at least 10 years.

### Plans to promote participant retention and complete follow-up 

Different measures will be implemented to ensure participant retention:Study data may be collected as part of a brief follow-up visit that does not significantly exceed the scope of routine out-of-study follow-up. The time points of the follow-up visits are selected in concordance with the routine control visits in the outpatient clinic after surgery, so that participants are not overburdened with additional appointments for study purposes.To improve patient adherence, all follow-up appointments are scheduled at the end of the previous appointment, and patients will be reminded of the appointment by phone or email one week before the scheduled appointment. A 15-day window, defined as 7 days before and 7 days after the due date, will be available to complete the 6-week and 29-day windows, defined as 14 days before and 14 days after the due date for the 6-month follow-up assessments and a 61-day window, defined as 30 days before and 30 days after the due date, will be available to complete the 12-month and 24-month follow-up assessments.

